## Abstract

**Aim:**

Despite the potential benefits of e‐health interventions for patients with psychosis, the integration of these applications into the clinical workflow and analysis of their long‐term effects still face significant challenges. To address these issues, we developed the ReMindCare app. This app aims to improve the treatment quality for patients with psychosis. We chose to study the app in real world and pragmatic manner to ensure results will be generalizable.

**Methods:**

This is a naturalistic empirical study of patients in a first episode of psychosis programme. The app was purpose‐designed based on two previous studies, and it offers the following assessments: (a) three daily questions regarding anxiety, sadness and irritability; and (b) 18 weekly questions about medication adherence, medication side effects, medication attitudes and prodromal symptoms. The app offers preset alerts, reminders and the ability for patients to reach out to their clinicians. Data captured by the app are linked to the electronic medical record of the patient. Patients will use the app as part of their ongoing care for a maximum period of 5 years, and assessments will occur at baseline and at the end of the first, second and fifth years of app use.

**Results:**

Recruitment started in October 2018 and is still ongoing.

**Conclusions:**

The ReMindCare app represents early real‐world use of digital mental health tools that offer direct integration into clinical care. High retention and compliance rates are expected, and this will in turn lead to improved quality of assessments and communication between patients and clinicians.

AbbreviationsAppapplicatione‐healthelectronic healthEMRelectronic medical recordFEPPfirst episode of psychosis programSQsatisfaction questionnaire

## INTRODUCTION

1

Early intervention programs for first‐episode psychosis are effective evidence‐based interventions that foster recovery, prevent disability and reduce costs associated with illness in both the short and long term (Arango et al., 2017). However, like all clinical programs, they face implementation challenges. Specific challenges identified by the RAISE study in the United States include workforce development, community activation, fidelity and measurement of outcomes and patient involvement (Dixon, 2017). In Spain, which has a non‐contributory health system financed through taxation and supported by public funding, universal health coverage and free health care services result in a lack of professionals, tools and financial support to properly deliver these interventions (Arango et al., 2017). Thus, interventions that reduce the number of consultations and hospital admissions, enhance interview efficiency, increase the early detection of illness and enhance treatment efficacy are highly encouraged (Arango et al., 2018; MSCBS, 2019). Research on smartphone ownership among youth receiving early intervention services suggests that, like the rest of the population, they increasingly own these devices; a 2015 study suggested 81% ownership (Lal et al., 2015), and more recent research studies suggested 85% (Aref‐Adib et al., 2016) to 86% (Bonet et al., 2018) ownership. Furthermore, many studies have found high percentages of interest (70%‐80%) in e‐health interventions among these patients (Bonet et al., 2017; Firth et al., 2016; Gitlow et al., 2017), with no differences related to demographic or clinical characteristics (Berry, Lobban, Emsley, & Bucci, 2016; Bonet et al., 2018).

Thus, in this digital age, it is not surprising that those with psychosis are already turning to the internet and their smartphones for information about their illness, peer support and local treatment resources (Aref‐Adib et al., 2016; Torous & Keshavan, 2018), creating an opportunity for community engagement by using early intervention programs. Perhaps, the greatest potential for digital technology for early intervention programs is achieving fidelity and measurement of outcomes through automatically quantifying patients' treatment trajectory through real data, captured via surveys and sensors delivered via patients' phones. Numerous studies have shown the feasibility and acceptability of remotely monitoring location via smartphones and how such data can be used to predict risk and stratify patients with schizophrenia (Barnett et al., 2018; Bucci et al., 2018; Wang et al., 2016). By capturing and quantifying the lived experiences of those with psychosis, digital technology can help early intervention programs measure functional recovery metrics, such as employment, social support and medication adherence, in addition to subjective metrics.

However, despite the potential of digital technology to augment early intervention care, efforts to date have been largely composed of brief feasibility studies rather than actual clinical integration projects. Most interventions analysed have been implemented in periods ranging from 1 to 78 weeks, with the majority only implemented for 4 weeks or less (Berry et al., 2016; Bonet et al., 2017). A second limitation is the feasibility of translating these interventions into daily clinical practice, which has not been properly tested, as many studies were not designed to be implemented in the hospital or clinical workflow (Lauckner & Whitten, 2016; Zanaboni et al., 2018). Moreover, some studies suggested that, to achieve full integration into clinical practice, organizations also need to adapt their systems to these technologies; otherwise, success of the interventions would be harmed (Appelbaum & Wohl, 2000). A third limitation is the impact of digital health interventions on clinicians' workload and clinical efficiency remains understudied (Gitlow et al., 2017; Hoerbst & Schweitzer, 2015; Zanaboni et al., 2018). Finally, it is also important to consider patients' perspectives outside of clinical studies. Although the majority of studies found high levels of acceptance among patients in terms of participation in e‐health interventions (Berry et al., 2016; Bonet et al., 2018), some studies have indicated that excessive e‐health communications could be regarded as repetitive, intrusive or irritating (Kannisto, Adams, Koivunen, Katajisto, & Välimäki, 2015; Palmier‐Claus et al., 2013) or could increase worries about illness (Kannisto et al., 2015). Thus the pragmatic and real world nature of our study offers broad generalizable knowledge that considers not only how the app may impact care but also how it can be implemented into care.

The potential of digital mental health for early course psychosis stands in sharp juxtaposition to the limited real‐world clinical evidence for its impact, integration and acceptability among both patients and clinicians. To address these issues and improve the quality of early intervention programs in patients with a first episode of psychosis, we have developed an application (app) called “ReMindCare.” The ReMindCare app was created as a tool that could be integrated into standard psychiatric care and treatment, filling the gap between research and clinical practice.

## METHODS

2

### Study objectives

2.1

The main objective of this study is to address whether the introduction of the ReMindCare App into daily clinical practice improves the quality of treatment for patients in a first episode of psychosis programme (FEPP).

Specifically, the aims of the study are (1) to assess the effectiveness of the ReMindCare app, in terms of improvement of adherence to anti‐psychotic medication, early detection of relapses and improvement of communication with clinicians, vs treatment as usual in patients with a psychotic disorder; (2) to analyse the use of the ReMindCare app by the patients in terms of rates of adherence, compliance, alerts generated and the total time using the app; and (3) to assess the satisfaction of patients with using the app and the perceived usability of the ReMindCare app.

### Study design

2.2

In the protocol, we describe the ReMindCare intervention as the first prospective naturalistic and empirical study of an app for FEPP. This app aims to improve the quality of the evaluation and treatment of patients. At the time of submitting this article, ReMindCare had been introduced as a clinical tool into daily psychiatric practice for more than a year. However, enrolment of patients continues, and the first analysis of the data will be conducted by March 2020.

### Study setting

2.3

The ReMindCare app was systematically integrated into the daily FEPP workflow at the Public Clinical Hospital of Valencia (Spain), where it is currently being used. This FEPP is a free care service that aims to enhance the quality of the early care of outpatients with a first episode of psychosis, from the early phases of the illness through the first five critical years of treatment (Arango et al., 2017).

Given the pragmatic and naturalistic nature of this study, no remuneration or compensation is offered to patients participating in the programme or using the app. Rather, the app is offered as an additional and free service to the patients in treatment at study sites.

### Participants

2.4

#### Recruitment and enrolment

2.4.1

Every outpatient from the FEPP who meets the criteria for inclusion is considered a potential user of the ReMindCare app. Once patients enrol in the study, they are able to use the app for a maximum period of 5 years, which is the time when they would be discharged from the FEPP.

All patients interested in using the app must sign an informed consent form and must complete some baseline assessments before their inclusion in the study.

#### Eligibility criteria

2.4.2

To be considered for this study, patients must be accepted into the FEPP at the Clinical Hospital of Valencia. Criteria for inclusion in the FEPP are:Diagnosis of psychotic disorder following DSM‐5 (APA, 2013) criteria, interview conducted by a licensed clinician.Less than 5 years of illness duration.Residence associated with the hospital area of correspondence (Area 5 of Valencia).Age between 17 and 65 years oldOwnership of a smartphone with an internet connection that allows the proper installation and functioning of the app.

Exclusion criteria include the following:Inability to use and master a mobile device and the Internet.Refusal to sign an informed consent form.Spanish/English language fluency limiting ability to partake in clinical conversations or to understand the app questionnaires.

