### Data collection and measures

2.6

An overview of all included measures and assessment points is included in Table 1.

**TABLE 1 eip12960-tbl-0001:** Study measures and assessment times

Timepoint	ReMindCare intervention					
	Baseline	Intervention			Follow‐up	
	*t* _0_	*t* _1_	*t* _2_	*t* _3_	*t* _4_	*t* _5‐8_
Enrolment						
Eligibility screen	X					
Informed consent	X					
Assessments						
Baseline assessment						
Clinical Global Impression Scale (CGI) (Busner & Targum, 2007)	X				X	X
Global Assessment of Functioning (GAF) (Endicott, Spitzer, Fleiss, & Cohen, 1976)	X				X	X
Positive and Negative Syndrome Scale (PANSS) (Peralta & Cuesta, 1994)	X				X	X
Premorbid Adjustment Scale (PAS) (Cannon‐Spoor, Potkin, & Wyatt, 1982)	X				X	X
Drug Attitude Inventory (DAI‐10) (Hogan, Awad, & Eastwood, 1983)	X				X	X
Beck Cognitive Insight Scale (BCIS) (Beck, Baruch, Balter, Steer, & Warman, 2004)	X				X	X
Sociodemographic information (Age, sex, ethnicity, marital status, level of education, living situation and employment status)	X					
Clinical information (Diagnose, years of illness, pharmacological treatment, suicidal attempts, history of illness)	X		X		X	X
Outcome measures						
Simplified Medication Adherence Questionnaire (SMAQ) (Morisky, Green, & Levine, 1986)	X		X		X	X
Number of relapses	X		X		X	X
Number of visits to urgent care units at the hospital	X		X		X	X
Number of hospital admissions	X		X		X	X
ReMindCare measures						
Answers to questionnaires		X	X		X	X
Quantity of “urgent consultation” requests		X	X		X	X
Quantity of alarms generated		X	X		X	X
Satisfaction Questionnaire^†^				X		X

Note: *t*
_1_ = introduction of the ReMindCare app into clinical practice; *t*
_2_ = first‐year preliminary data assessment; *t*
_3_ = focus group, first year; *t*
_4_ = second‐year follow‐up; *t*
_5‐8_ = fifth‐year follow‐up; Satisfaction questionnaire^†^ = App feedback questionnaire made for the purpose of this research.

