Baseline surveys, including clinical and sociodemographic information and clinical standardized questionnaires, were administered before the enrolment of the patient in the study. As shown in Table 1, data regarding the main outcomes, such as adherence to medication, number of relapses, number of visits to the hospital urgent care units and number of hospital admissions, will be collected and analysed at the end of the first, second and fifth years of the intervention. Moreover, information generated for patients through the use of the app will also be analysed at the same timepoints. Finally, to analyse the feedback of patients regarding the use of the app, we plan to conduct focus groups at the end of the first year of the intervention, and we have also designed a “satisfaction questionnaire” (SQ) that patients will complete at the end of the first year of the intervention or before discontinuing the use of the app (if discontinuation occurs before the first year of app usage). This SQ was made for the purpose of this research study and is based on previous satisfaction and usability questionnaires, such as the user version of the Mobile Application Rating Scale (uMARS) (Stoyanov, Hides, Kavanagh, & Wilson, 2016), the System Usability Scale (SUS) (Brooke, 1996), EnLight: a tool for mobile and web‐based eHealth interventions (Baumel, Faber, Mathur, Kane, & Muench, 2017) and the App Quality Evaluation (AQEL) (DiFilippo, Huang, & Chapman‐Novakofski, 2017). This questionnaire is displayed in Appendix B.

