### Planned data analysis

2.7

Descriptive analyses of sociodemographic and clinical variables will be conducted. A multivariate data analysis will be carried out to explore relationships between sociodemographic and clinical variables and adherence to treatment and ReMindCare measures. An ANOVA model of repeated measures will be used for the main research outcomes. All analyses will be conducted with an alpha set at *P* < 0.05.

These preliminary quantitative data analyses and the preliminary results regarding patient compliance, retention rate and perceived satisfaction with the use of the ReMindCare app are expected by the end of the first year of using the app (March 2020). At that time, qualitative analyses of data are also planned.

Subsequent analysis of the data will be conducted at the end of the second and fifth years of use of the app.

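### With no minimum time since onset at entry, baseline admissions and urgent visits can include the first episode, so before-after counts can fall without any app effect

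*Protocol article*

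**What the plan says.** **Entry.** Section 2.4.2 requires a DSM-5 psychotic disorder and "Less than 5 years of illness duration". This is an upper limit only, and no interval since onset or since the last episode is asked for. Section 2.4.1 adds: "Every outpatient from the FEPP who meets the criteria for inclusion is considered a potential user of the ReMindCare app". Section 2.3 describes the programme as running "from the early phases of the illness through the first five critical years of treatment". New and established patients are therefore both eligible.

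**Outcomes.** Table 1 lists "Number of visits to urgent care units at the hospital" and "Number of hospital admissions" as outcome measures, marked at baseline and at the first-, second- and fifth-year assessments. Section 2.6 places both among the main outcomes, which "will be collected and analysed at the end of the first, second and fifth years of the intervention".

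**Analysis.** Section 2.7 states: "An ANOVA model of repeated measures will be used for the main research outcomes". Alpha is 0.05.

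**Comparator.** Section 2.1 frames effectiveness against treatment as usual. Section 4.2 says the study is neither randomised nor controlled, but plans to compare main outcomes between users and controls matched on age. It concedes that the groups may differ.

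**The concern.** A first psychotic episode often brings an urgent-care visit, an admission or both. A patient who joins the programme and starts the app shortly afterwards carries that hospital use in the baseline count, and the next year cannot contain the same event again. The group mean is raised at baseline by patients captured near a peak and then returns towards their usual level.

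Equal counting windows would not cure this, and neither would replacing ANOVA with a count model. The cause is when patients enter relative to the episode.

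At stake is the reading of a before-after drop in admissions or urgent visits. Section 4.1 anticipates fewer of both. A drop that comes from the timing of enrolment could be credited to the app.

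**Working it through.** The article states no event rate, no share of recent entrants and no sample size, so there is no figure of its own to reproduce. Section 3 gives 57 patients enrolled so far, which is a count and not a target. Everything below is illustrative and uses assumed inputs.

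**Inputs (assumed)**
- f, the share of users whose baseline window contains the first episode: 0.20 to 0.50. The lower value is what an even spread of illness duration over 0-5 years gives for the first year (1/5 = 0.20).
- p, the share of those admitted for that episode: 0.50 to 0.70.
- b, admissions per year otherwise: 0.2, unchanged by the app.
- Equal one-year windows before and after entry. Year-1 mean = 0.20 throughout.

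**Model A: every patient has the background rate before entry, and recent entrants have the index admission on top.** Baseline = b + f·p.
- f = 0.20, p = 0.50: 0.2 + 0.10 = 0.30; fall 0.10/0.30 = 33%.
- f = 0.30, p = 0.50: 0.2 + 0.15 = 0.35; fall 0.15/0.35 = 43%.
- f = 0.50, p = 0.70: 0.2 + 0.35 = 0.55; fall 0.35/0.55 = 64%.

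**Model B: recent entrants have no admissions before the index one, because they were not yet ill.** Baseline = (1 − f)·b + f·p.
- f = 0.20, p = 0.50: 0.16 + 0.10 = 0.26; fall 0.06/0.26 = 23%.
- f = 0.30, p = 0.50: 0.14 + 0.15 = 0.29; fall 0.09/0.29 = 31%.
- f = 0.50, p = 0.70: 0.10 + 0.35 = 0.45; fall 0.25/0.45 = 56%.

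Across both models the apparent fall runs from 23% to 64%.

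**Chance of a significant result with no app effect.** This was simulated with 4,000 runs, n = 57, Poisson background and s = f·p extra baseline events per patient, as in Model A. The test was a paired t-test, which equals a two-time repeated-measures ANOVA, two-sided at 0.05.

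| s | b = 0.2 | b = 0.4 |
|---|---|---|
| 0 | 4% | 5% |
| 0.1 | 18% | 12% |
| 0.2 | 51% | 33% |
| 0.3 | 82% | 60% |

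Model B gives a smaller mean shift for the same f and p, so these figures should not be carried over to it.

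**With controls.** Change in users against change in controls, 57 v 57, b = 0.3, no app effect:
- s = 0.5 in both groups: 5% significant.
- s = 0.5 v 0.3: 21%.
- s = 0.5 v 0.1: 69%.
- s = 0.1 v 0.5: 68%, with the bias now running against the app.

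The artefact cancels only when both groups carry the same share of recent episodes.

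**If the index episode is deleted from the baseline.** Under Model B, baseline = (1 − f)·b.
- f = 0.30: 0.14 against 0.20 in year 1, a rise of 0.06/0.14 = 43%.
- f = 0.50: 0.10 against 0.20, a rise of 0.10/0.10 = 100%.

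Deletion replaces a spurious fall with a spurious rise.

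**The case against.** **The before-after change is not the whole inference.** Section 2.1 sets the aim against treatment as usual, and section 4.2 plans a control comparison while admitting that the groups may differ. This stands, and it limits the point. What remains is that matching is on age alone, and age does not fix time since onset.

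**The hospital-use hypothesis in section 4.1 is about engagement.** It expects lower use among more engaged patients, and it compares those who did and did not use the urgent-consultation function. The explicit baseline-to-year-1 predictions concern the SMAQ and BCIS scores. This is fair. The before-after reading of admissions comes from Table 1 with the ANOVA sentence in section 2.7, and those do cover admissions and urgent visits.

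**The criteria do not select on a recent event.** A reader might infer that every baseline contains the qualifying episode. The documents do not support that. Eligibility asks for a diagnosis and a duration, not a recent admission. Patients some years into illness dilute the effect, and not every first episode leads to hospital use. The article also states no counting rule, and a condensed article may leave that to the full protocol. The point therefore holds for recent entrants under a look-back that ends at enrolment and reaches the episode. It is not shown for the whole cohort.

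**Years 1, 2 and 5 are not comparable.** A reader might infer this too. The article does not establish it: each patient has their own baseline, and only the mix of patients contributing at each time may shift.

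**Conclusion.** The concern holds in a limited form. The entry rule, the baseline counts and the repeated-measures analysis together allow a fall in mean admissions and urgent visits that owes nothing to the app. The direction follows from the design whenever some users enter soon after an episode that brought hospital use.

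The size cannot be read from the document. The 23-64% range rests on assumed shares, an assumed background of 0.2 admissions a year, and the choice of whether newly ill patients had any admissions before the index one. The arithmetic is for admissions. Urgent visits follow the same logic, but no separate figures are available. The control comparison protects the conclusion only to the extent that users and controls are alike in time since onset.

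This is a cheap improvement to make before any claim of reduced hospital use. It does not show that the study cannot answer its question.

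**What to change.** In sections 2.6 and 2.7:

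1. Count admissions and urgent visits over equal windows before and after entry, for example 12 months each. This makes the counts comparable in length but does not by itself remove the artefact.
2. Report the change separately for patients enrolled within 12 months of illness onset and for those enrolled later, using the years-of-illness variable already in Table 1.
3. Match or adjust the controls on illness duration as well as age.
4. State that no claim of reduced hospital use will rest on the uncontrolled before-after change in recent-onset patients.

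Do not simply remove the index episode from the baseline count. Newly ill patients would be left with a near-zero baseline, and the change would be biased the other way.

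The cost is some wording and the use of data already recorded. The price is smaller subgroups, a harder match and a less favourable before-after difference.

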#### Discontinuation and withdrawal

2.4.3

A patient's participation in the study will be discontinued if:The patient provides an explicit notification of not wishing to continue using the app.Lack of use the app for a period longer than 2 months after having been contacted by the research group over that period of inactivity.Discharged from the FEPP or if their consent is revoked.Given the naturalistic nature of this study, in case of discontinuation or withdrawal, patients will continue with the usual psychiatric treatment at the hospital.

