### Anticipated results

4.1

On the basis of previous studies (Bonet et al., 2017; Firth et al., 2016; Gitlow et al., 2017) that confirmed the interest of patients with psychosis in e‐health interventions and based on the high interest in owning an e‐health app that we found in our survey study (Bonet et al., 2018), we expect an acceptable retention rate (beyond 70%).

Moreover, based on previous studies (Ben‐Zeev et al., 2014; Ben‐Zeev, Kaiser, & Krzos, 2014; Brenner & Ben‐Zeev, 2014; Kimhy, Vakhrusheva, Liu, & Wang, 2014; Macias et al., 2015) that found rates of response to the communications of e‐health apps to be higher than 70%, we also expect moderate compliance with the app's communications (beyond 70%).

Furthermore, as previous studies have stated that electronic assessments are valid and reliable measures (Brenner & Ben‐Zeev, 2014; Kimhy et al., 2014; Palmier‐Claus et al., 2013; Spaniel et al., 2008), and based on preliminary perceptions obtained from the first 7 months of the current intervention, we expect that the use of the ReMindCare app would produce the following differences in the treatment of psychotic disorders:
*Improved quality of treatment delivery for clinicians*: Graphics of daily and weekly questionnaires allow clinicians to rapidly assess the status of the patient and to specifically orient their interactions with the patient to problematic areas. An improvement in the quality of evaluation is also expected. Perceptions of the clinicians regarding these issues will be qualitatively assessed in focus groups.
*Improved insight about the illness and mental health status for patients*: Sharing with patients their responses to the app is expected to increase accuracy of information and to decrease bias in this process. Moreover, it is expected that, by discussing their app responses with the patients, insight about their illness and their health status will increase. These perceptions will be mainly assessed by the “satisfaction questionnaire” (SQ), and they will also be assessed qualitatively in focus groups. Moreover, changes in insight between baseline and 1 year of intervention will be assessed by using the BCIS (Beck et al., 2004).

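### Stopping the app ends study participation without revoked consent, and no collection of the main outcomes is provided for afterwards, although the patient stays in the hospital's care

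*Protocol article*

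**What the plan says.** Section 2.4.3 (Discontinuation and withdrawal) opens its list with "A patient's participation in the study will be discontinued if". The grounds are:

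- "The patient provides an explicit notification of not wishing to continue using the app"
- "Lack of use the app for a period longer than 2 months after having been contacted by the research group" (the sentence goes on to tie the contact to that spell of inactivity)
- "Discharged from the FEPP or if their consent is revoked"

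The section then says that "in case of discontinuation or withdrawal, patients will continue with the usual psychiatric treatment at the hospital".

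Section 2.6 (Data collection and measures) names the main outcomes as "adherence to medication, number of relapses, number of visits to the hospital urgent care units and number of hospital admissions", collected at the end of years 1, 2 and 5. Adherence is measured with the SMAQ (Table 1). The only assessment that section 2.6 ties to early stopping is the satisfaction questionnaire, to be completed before the patient gives up the app.

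Section 4.1 (Anticipated results) expects retention beyond 70%. It also expects heavier users to have fewer treatment dropouts, relapses, admissions and urgent visits. Section 4.2 plans to compare users with age-matched controls.

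**The concern.** The rule makes giving up the app the same event as leaving the study. A patient who goes silent after being contacted has not revoked consent and is still treated at the hospital. Relapses, urgent visits and admissions are events in that care, and the SMAQ could be given at a routine visit. The article nevertheless describes no way for these outcomes to reach the data set.

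This matters most for aim 1 in section 2.1, effectiveness against treatment as usual. If patients who stop the app have worse outcomes, as section 4.1 predicts for low engagement, the before-after analysis is weighted towards the patients who do better. In the comparison with controls the loss falls on one side, because the article describes no equivalent exit rule for controls. The analyses in section 4.1 that relate engagement to relapse also lose outcomes at the low-engagement end, where they are needed.

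**Working it through.** The article gives no sample size calculation, event rate or power, so there is no stated figure to reproduce. The check is a reading of the text followed by an illustration of scale.

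**1. The text side by side**

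| Question | Where | Answer |
|---|---|---|
| What ends? | 2.4.3, opening line | Participation in the study |
| Must consent be revoked? | 2.4.3, last ground | No, that is a separate ground |
| Does the patient leave care? | 2.4.3, closing sentence | No, usual treatment continues |
| What is collected around early stopping? | 2.6 | Satisfaction questionnaire only |
| Are main outcomes collected afterwards? | 2.6 and Table 1 | Not provided for |
| Is engagement expected to relate to outcome? | 4.1 | Yes: more use, fewer relapses, admissions and dropouts |

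The article does not say outright that data collection stops. That follows from participation ending with no later collection described.

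**2. Number affected**

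Inputs: 57 enrolled so far (section 3) and the 70% retention floor (section 4.1).

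Stayers = 57 × 0.70 = 39.9, about 40. Leavers = 57 − 40 = 17. At 80% retention 11 would leave, and at 90% 6.

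**3. Relapse risk reported against true risk**

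Assumptions, none of them in the article: relapse risk of 20% in stayers; risk p in leavers, from 20% (no difference) to 50%; none of the leavers' relapses counted.

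True risk = (40 × 0.20 + 17 × p) / 57

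| p in leavers | True risk | Reported | Gap |
|---|---|---|---|
| 20% | (8 + 3.4)/57 = 20% | 20% | 0 points |
| 30% | (8 + 5.1)/57 = 23% | 20% | 3 points |
| 40% | (8 + 6.8)/57 = 26% | 20% | 6 points |
| 50% | (8 + 8.5)/57 = 29% | 20% | 9 points |

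**4. Comparison with controls**

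Assume the true risk is 30% in users and in controls alike, so the app has no effect. Let RR be the risk in leavers divided by the risk in stayers.

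Risk in stayers = 0.30 × 57 / (40 + 17 × RR)

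- RR 1: 17.1/57 = 30.0%, apparent benefit 0 points
- RR 1.5: 17.1/65.5 = 26.1%, apparent benefit 3.9 points
- RR 2: 17.1/74 = 23.1%, apparent benefit 6.9 points
- RR 3: 17.1/91 = 18.8%, apparent benefit 11.2 points

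The direction depends on RR being above 1. Section 4.1 expects this but gives no data for it.

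**The case against.** The strongest reply is that the loss of outcomes is an inference. Section 2.4.3 does not say that collection stops or that data already gathered are discarded. The article condenses a fuller protocol, and section 4.1 intends to relate engagement to dropouts and relapses, so some outcome data on poor engagers must be wanted. This stands as a caution. It does not remove the point: the rule as printed ends participation, section 2.6 provides for early stoppers only through the satisfaction questionnaire, and no analysis plan can recover a questionnaire that was never given.

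A second reply also has force. If a relapse or admission causes the silence, it happens while the patient is still a participant. It is lost only if events are not tallied up to exit. The illustration counts none of the leavers' relapses and is a worst case in that respect; tallying events to exit, with time at risk taken into account, would narrow the gap.

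Third, people stop apps for reasons unrelated to relapse. The Introduction notes that some patients find such messages intrusive or irritating. With equal risks there is no bias.

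A reader might also infer several stronger things that the article does not support:

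- **That the bias always favours the app.** No reasons for stopping are reported, and the link between engagement and relapse is an expectation.
- **That the results describe only satisfied, stable users.** Section 2.6 asks early stoppers for the satisfaction questionnaire.
- **That the repeated-measures ANOVA discards leavers.** Section 2.7 says nothing about missing data.
- **That non-responders drop out of the compliance denominator.** None is defined, and retention and total time of use are also analysed.
- **That losses can be compounded to years 2 and 5.** The 70% is a floor with no stated time unit, and enrolment continues.
- **That two silent months alone suffice.** The rule needs more than 2 months and contact by the research group.

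**Conclusion.** The point holds as a defect of a fixed design rule. Study participation is tied to app use, and the main outcomes are not provided for once use stops, although consent stands and the patient remains in the same hospital's care. On the article's own expectation the loss is likely to be informative, and it is expected, though not certain, to favour the app in both the before-after analysis and the comparison with controls.

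Its size cannot be fixed from the article. At the retention floor, 17 of 57 patients is the scale. Under the stated assumptions the gap in relapse risk runs from nothing to about 9 points. The non-randomized comparison is already acknowledged as a limitation in section 4.2, but one-sided loss is a further and avoidable source of bias. Aim 2, on use of the app, is less affected, because stopping is itself one of its results.

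**What to change.** Split section 2.4.3 into two events:

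1. **Discontinuation of app use**, recorded with date and reason.
2. **Withdrawal from the study**, when consent is revoked.

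After discontinuation of app use, keep collecting relapses, urgent visits and admissions from hospital records, and the SMAQ at routine visits, at years 1, 2 and 5 for as long as the patient remains in the first-episode programme. After discharge from the programme, use record-based outcomes only, where available, since a routine visit for the SMAQ cannot be assumed. Analyse the main outcomes in all enrolled patients, regardless of app use. If the sponsor already follows these patients, the section should say so.

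The cost is amended protocol and consent wording and some record extraction. Clinical handling of inactive patients need not change. The results may look less favourable. Enrolment is still open, so later outcomes can still be kept; questionnaire data missed in the meantime cannot be recovered.
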